## Abstract

**Background:**

Acute lymphoblastic leukemia (ALL) is the most common malignancy diagnosed in children. At present, the long-term survival from pediatric ALL is well over 90%. However, the probability of event-free survival is reduced if the lumbar puncture (LP) procedures at the beginning of the patient’s intrathecal therapy cause blood leakage into the spinal canal and blast cells contaminate the cerebrospinal fluid. According to the literature, such traumatic LP procedures concern one out of five pediatric patients with ALL.

Recently, a novel medical device measuring the tissue bioimpedance at the tip of a spinal needle was found feasible in pediatric patients with ALL. The LP procedure was successful at the first attempt in 80% of procedures, and the incidence of traumatic LPs was then 11%. The purpose of the present study is to compare the bioimpedance spinal needle system with the standard clinical practice resting on a conventional spinal needle and investigate its efficacy in clinical practice.

**Methods:**

The study is a multicenter, randomized, two-arm crossover noninferiority trial of pediatric hemato-oncology patients that will be conducted within the usual clinical workflow. Patients’ LP procedures will be performed alternately either with the IQ-Tip system (study arm A) or a conventional Quincke-type 22G spinal needle (study arm B). For each enrolled patient, the order of procedures is randomly assigned either as ABAB or BABA. The total number of LP procedures will be at least 300, and the number of procedures per patient between two and four. After each study LP procedure, the performance will be recorded immediately, and 1-week diary-based and 4-week record-based follow-ups on symptoms, complications, and adverse events will be conducted thereafter. The main outcomes are the incidence of traumatic LP, first puncture success rate, and incidence of post-dural puncture headache.

**Discussion:**

The present study will provide sound scientific evidence on the clinical benefit, performance, and safety of the novel bioimpedance spinal needle compared with the standard clinical practice of using conventional spinal needles in the LP procedures of pediatric patients with leukemia.

**Trial registration:**

ISRCTN ISRCTN16161453. Registered on 8 July 2022.

## Background

Acute lymphoblastic leukemia (ALL) is the most common malignancy diagnosed in children showing the peak incidence around 3–5 years of age [1]. The incidence of ALL is about 20–40 cases per million children and adolescents aged under 18 years old, depending on the geographic region (2). In developed countries, the improved survival from ALL has been a real success story during the last few decades, and at present, the long-term survival from ALL is well over 90% [1, 2].

Intrathecal chemotherapy administered by lumbar puncture (LP) is an essential part of ALL treatment. Besides the intrathecal therapy, the collected samples of cerebrospinal fluid (CSF) provide important information for the diagnosis, risk assessment, and choice of the patient’s treatment path as well as for the follow-up. Depending on the personalized risk classification, the total number of LP procedures may vary from five to more than 20 procedures during the roughly 2-year treatment period of ALL [3]. Regarding the patient’s optimal treatment and recovery from ALL, the successful and smooth conduct of the LP procedure throughout the treatment is of paramount importance.

The patient’s event-free survival reduces if the LP procedures at the beginning of the patient’s intrathecal therapy are traumatic and blast cells contaminate CSF because of blood leakage caused by a needle trauma [4–10]. Traumatic LPs (TLP), defined as a concentration of red blood cells in the CSF sample above a specified threshold, are frequent in clinical practice. In hemato-oncology, the threshold for TLP is at least 10 erythrocytes/μL of CSF. Compiling the reported data from almost 22,400 LP procedures of pediatric oncology patients [4–14], the mean incidence of TLP is about 20%, while the study-specific incidences of TLP vary from 1% [8] to 37% [13]. Without blood leakage into the subarachnoid space, there should not be any erythrocytes in CSF.

In pediatric patients, a higher number of attempted punctures during a single LP procedure is associated with a doubled risk of TLP [15]. However, one cannot presume constant success at the first attempt. In pediatric patients with ALL, the mean first puncture success rate of LP with a single skin penetration is good to excellent varying from 70% up to 95% [16–19]. In adults with leukemia, high success at the first attempt is associated with a roughly halved incidence of TLP [20], whereas in pediatric patients with ALL, the probability of TLP was about fourfold if the first attempt was not successful [19]. High success at the first attempt likely contributes also to a low incidence of post-dural puncture headache (PDPH) [17], which is the most considerable adverse event after an LP procedure. In children with ALL, however, the incidence of PDPH is yet relatively low varying around 10% [15–19].

Experience and training contribute to an improved performance in LP [17, 18]. The success of the LP procedure can also be improved by image guidance either before inserting the spinal needle into the body or in real-time during the procedure. According to recent meta-analyses [21–23], ultrasound guidance is associated with a halved incidence of TLPs, an improved success rate of LP procedures, and a reduced incidence of failed procedures compared to the traditional palpation-based procedures. Particularly patients with high body mass index (BMI), anatomic abnormalities, young age, or a history of many failed attempts may be referred to ultrasound imaging before or during the LP procedure [21, 24].

While the evidence for the clinical utility of ultrasound imaging in performing LP is convincing [21–23], the true real-time ultrasound guidance requires a physician’s one hand to use the ultrasonic probe and the other to advance the spinal needle, let alone the need for bedside imaging equipment, and provider’s adequate proficiency to employ ultrasound imaging and interpret the images in real-time. These requirements may modify the standard provision of LP the physicians who are accustomed to performing. Thus, a needle guidance method not requiring specific expertise and simultaneous operation of the imaging equipment but still providing real-time feedback on the needle tip location would be a valuable option.

Recently, clinical studies of adults [25], neonates and infants [26], and pediatric patients with ALL [19] showed the feasibility and safety of a novel bioimpedance-based spinal needle system in LP procedures. This system, called the IQ-Tip system, measures bioimpedance at the tip of the spinal needle with 15 different frequencies and classifies the bioimpedance data 200 times in a second. This means that the tissue classification is virtually real-time (performed at every 5th ms) and the spatial sensitivity is high (~ 1 mm^3^). The system gives an audio-visual alarm when the needle tip reaches CSF in the subarachnoid space and indicates the correct location for CSF sampling or administration of intrathecal therapy. In our recent single-arm study of pediatric patients with ALL, the first attempt was successful in 80% of procedures, and the incidence of TLP was 17%. Further, neither the success rate nor the incidence of TLP was associated with the provider’s experience or the patient’s overweight [19].

Given the promising real-world clinical experience, we hypothesize that the performance of the IQ-Tip system is at least comparable to the conventional spinal needle regarding the incidence of TLP in LP procedures of pediatric hemato-oncology patients. The primary objective of the present trial is to demonstrate that the observed incidence of TLP with the IQ-Tip system will indicate either noninferiority or not only noninferiority but also superiority compared to the conventional spinal needle, which is the current standard clinical method. The secondary objectives are to compare the first puncture success rate and the incidence of complications, particularly the incidence of PDPH, in the LP procedures performed with the IQ-Tip system and conventional spinal needle. No formal hypotheses are set for the secondary outcomes.

## Materials and methods

### Trial design and setting

The present study (acronym IQ-LP-04) is a multicenter, randomized, two-arm crossover noninferiority trial of pediatric hemato-oncology patients. Since the patients act as their controls in the cross-over design, the potential bias due to variability between the patient characteristics is effectively controlled for. The two study arms refer to performing the patient’s LP procedures alternately using the IQ-Tip system (study arm A) or a conventional spinal needle (study arm B). The arm of the first study procedure will be randomly assigned, while the number of procedures per patient will be between two and four. Thus, the two possible randomly assigned sequences of the study LP procedures are ABAB and BABA.

All study LP procedures are part of patients’ preplanned LP procedures without additional procedures or laboratory tests. Only the data needed for the management of patients’ malignant diseases will be collected as part of routine therapy and evaluation, independent of the present trial. Biological specimens for genetic or molecular analyses will not be collected. If the patient’s treatment or medical condition requires concomitant care, modification, or other interventions during the study, they will be permitted. The crucial point for the study is that the allocated spinal needles are used in the study LP procedures as intended. Patients’ treatments and care will continue as planned after completing the trial or withdrawing from the study due to any reason. There are no specific plans for promoting participant retention during the study. The pragmatic nature of the present trial is expected to promote complete follow-up and acquisition of data.

After each study LP procedure, there will be a 1-week follow-up using a symptom diary and a 4-week follow-up of hospital electronic health records. The flow chart of the study LP procedures is shown in Fig. 1, whereas the schedule of enrolment, study LP procedures, and assessments during the post-allocation period are outlined in Table 1. This protocol has been written according to the SPIRIT reporting guidelines [27] and verified against the SPIRIT checklist.

**Fig. 1 Fig1:**
[figure not shown]
The flow chart of the study LP procedures

**Table 1 Tab1:** Schedule of enrolment, interventions, and assessments (only those assessments pertinent to the efficacy analysis are presented) during the post-allocation period of the trial

Study period	Enrolment		Post-allocation												Close-out
**Time point**	*t*_−1_	*t*_0_	*t*_1_	*t*_1_ + 1wk	*t*_1_ + 4wk	*t*_2_	*t*_2_ + 1wk	*t*_2_ + 4wk	*t*_3_	*t*_3_ + 1wk	*t*_3_ + 4wk	*t*_4_	*t*_4_ + 1wk	*t*_4_ + 4wk	*t*_x_
**Enrolment**															
Eligibility assessment	x														
Informed consent	x														Archived
Random allocation		x													
**Interventions**															
LP procedure sequence ABAB			A			B			A			B			Tx continues as planned
LP procedure sequence BABA			B			A			B			A			
**Assessments**															
Baseline variables															
Age		x													
Height		x													
Weight		x													
Sex		x													
Main outcome variables															CRFs archived
Incidence of TLP			x			x			x			x			
First puncture success rate			x			x			x			x			Pseudonymized copies of CRF are delivered to the sponsor
Incidence of PDPH				x			x			x			x		
Other outcome variables															CRFs archived
Peripheral blood analysis			x			x			x			x			
CSF analysis			x			x			x			x			Pseudonymized copies of CRF are delivered to the sponsor
Number of LP attempts			x			x			x			x			
Number of failed procedures			x			x			x			x			
Symptoms, complications, and adverse events				x	x		x	x		x	x		x	x	

The study will be conducted in pediatric hemato-oncology departments of five Finnish university hospitals located in Helsinki, Kuopio, Oulu, Tampere, and Turku. These hospitals provide tertiary care for the entire Finnish population of about 5.6 million people. They are also responsible for the medical care of all childhood cancer patients living in their catchment areas.

The participating hemato-oncology departments are called the investigational sites, where the local principal investigators are responsible for conducting the study. All study LP procedures will be conducted within the daily clinical routine of the investigational sites. As the study procedures are part of the patient’s planned therapy for malignant disease, they will be covered by the hospital’s liability insurance. The study sponsor, a Tampere-based manufacturer of the IQ-Tip system (www.injeq.com), has liability insurance for covering the serious adverse events or harms affecting the participant that will be attributed to the IQ-Tip system.

### Ethical and regulatory considerations

The study protocol has been approved by the Regional Ethics Committee of the Expert Responsibility Area of Tampere University Hospital, Finland (date 10/05/2022, R22039L). The National Competent Authority (Fimea, Helsinki) evaluated and approved (date 04/07/2022) the study as per the national legislation. The trial will be conducted according to Helsinki Declaration and Good Clinical Practice (ISO 14155:2020).

A need to change some procedures in the study protocol may arise during the study. Should this happen, the principal investigator and the sponsor representatives will scrutinize the need and decide whether the protocol amendments are justified and necessary. If so, Ethics Committee and National Competent Authority will be notified about these amendments for approval before their implementation in the protocol.

### Registration

The trial has been registered on ISRCTN registry (date 08/07/2022, ISRCTN16161453). All items presented in the trial registration data set are also addressed within this protocol article.

### Recruitment and consent

Local study nurses or investigators will recruit participants in this trial among pediatric hemato-oncology patients of the investigational sites. All patients whose malignant disease requires multiple LP procedures in diagnostics or therapy are potentially eligible for the study. After having received written and oral information about the trial, the patient and/or parents may express their willingness to participate, sign the written informed consent, and give it to the recruiting person.

The consent applies to the use of all collected data in a pseudonymized form in scientific research, product development, and communication with authorities in potential safety and regulatory issues. Except for those mentioned in this protocol, there are no plans for ancillary studies.

The original participant’s trial information leaflet and the informed consent form, approved by the ethical committee and competent authority, are in Finnish and thus not given as supplementary material. In short, the leaflet describes the purpose and contents of the study; benefits and risks related to the study; principles of data protection, processing, and handling; voluntariness; statements of existing liability insurances and lack of incentives; and dissemination plans for the trial results.

A patient will be eligible for the trial, if:He/she is older than 1 year but no more than 18 years at the beginning of the study.His/her diagnosis or treatment plan requires multiple LP procedures for collecting CSF samples and injecting intrathecal therapy.The planned LP procedures will be performed with 22G Quincke-type spinal needlesThere are at least two LP procedures left in the patient’s treatment protocol.Both the parent(s) and the patient, depending on the patient’s age, give a signed informed consent before the first study LP procedure.

A patient will be excluded from the trial if:The parent(s) and/or the patient refuse to participate in the trial or the parent(s) and/or the patient are considered unable to give an informed consent.The provider considers the longest available spinal needle too short to perform the procedure safely.

An LP procedure of an otherwise eligible patient will be excluded from the study if:There is any temporary contraindication to LP, including but not limited to skin infection around the puncture area, unstable hemodynamics, bleeding tendency and increased intracranial pressure.

The final decision to include or exclude the patient or a single LP procedure (e.g., the initial procedure of the patient with ALL) will be up to the clinical judgement of the provider.

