### Randomization and allocation

The spinal needle that will be used in the patient’s first study LP procedure, either the IQ-Tip system (study arm A) or a conventional spinal needle (study arm B), was determined by block randomization before recruiting patients. Block randomization ensures an approximately even number of both sequences of study LP procedures (ABAB and BABA) in random order while eliminating the bias that may arise from a fixed order of LP procedures.

With a dedicated Matlab script, the sponsor has generated randomization lists for each investigational site beforehand (date 30/09/2022). The sponsor will also prepare and deliver enough sequentially numbered sealed envelopes containing the randomly assigned sequences (either ABAB or BABA) to the investigational sites. During the trial, the person who will perform the statistical analyses will not meet the participants nor be involved anyhow in collecting data or filling their case report forms (CRF).

Upon enrolling a new patient to the study, the next available envelope in the order will be opened to reveal the sequence of study LP procedures for the given patient. This sequence determines the choice of a specific Participant’s File, a binder that contains color-coded CRFs and other relevant documents for collecting the data from the four study LP procedures. The running number of the envelope together with the hospital-specific three-letter prefix will determine the patient’s pseudonym (ID code).

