### Procedures

The study LP procedures will be performed either with the IQ-Tip system (study arm A) or the conventional spinal needle (study arm B) according to the patient’s randomly allocated sequence. The personnel of the investigational sites will perform the study LP procedures within the usual clinical workflow. As a standard procedure, the LP procedures of pediatric patients with leukemia are performed under general anesthesia in the lateral decubitus position [19]. Because of general anesthesia, the patient is blinded to the allocated spinal needle. As both study needles are similar, the need for unblinding is deemed irrelevant.

Before starting the study, the sponsor’s representatives will give an overview of the Instructions for Use and a practical training session on the use of the IQ-Tip system to the local principal investigators ([name]), other physicians, and study nurses at the investigational sites. The attendees will also have the possibility to try the system on a lumbar phantom (Blue Phantom BPLP2201, CAE Healthcare, FL, USA). Later, the local principal investigators will be responsible for the training of new users of the system.

The above-described short training was employed in our previous single-arm study [19]. Immediately after that study, the usability of the IQ-Tip system was assessed with System Usability Scale (SUS) [28, 29]. In short, all 26 physicians who had performed at least one study LP procedure with the IQ-Tip system received an electronic SUS form, 20 of them (77%) responded anonymously. The mean SUS score was 75 (SD 13), which indicates good clinical usability and acceptability for the system.

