#### The LP procedure A

Study procedure A will be performed with the IQ-Tip system (Injeq Plc, Tampere, Finland), which is a CE-marked medical device as per Medical Device Regulations (MDR EU 2017/745) approved for any clinically indicated LP procedure. The system comprises either a 40-mm, 65-mm, or 90-mm-long 22G Quincke-type spinal needle (IQ-Tip spinal needle), a bioimpedance analyzer, and a thin, flexible coaxial cable for connecting the needle to the analyzer. The IQ-Tip spinal needle is identical to the conventional Quincke-type 22G spinal needle with a stylet, except the stylet is configured as a bioimpedance electrode and it has a cable connector at the handle end. The analyzer has an internal memory, where the raw bioimpedance data collected at a 200-Hz sampling rate will be stored for further post-hoc analysis.

Performing the LP procedure with the bioimpedance needle is basically like that with the conventional spinal needle. Also, the removal and reinsertion of the stylet do not differ from the conventional spinal needle. Only the cable at the handle end is the major difference.

When performing the LP procedure with the IQ-Tip system and perceiving the CSF detection alarm, the provider can either remove the stylet and check for CSF flow through the needle or continue the puncture upon clinical judgment on the location of the needle tip. Similarly, irrespective of the alarm, the provider can remove the stylet and check for CSF flow whenever considered necessary.

When the needle tip is correctly in the subarachnoid space verified by CSF flow, the provider will take the CSF sample and deliver the intrathecal therapy according to the patient’s treatment protocol.

Right after performing the study LP procedure with the IQ-Tip system, the provider will evaluate the performance and record the results concerning a successful procedure at the first attempt, number of attempts needed for a successful procedure, number of stylet removals in the successful procedure, failure to perform the procedure, and the accuracy of perceived alarms on the patient’s CRF. Also, patients’ immediate complications and device deficiencies, if any, will be recorded on CRF.

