**Fig. 2 Fig2:**
[figure not shown]
Schematic on the relation between the numbers of traumatic LP procedures (TLP) with the IQ-Tip system and conventional spinal needle required to indicate noninferiority (green area) or not (red area)

The primary statistical comparison of outcome variables will be based on the true use of the allocated spinal needles in the study LP procedures. Therefore, per-protocol analysis will be employed in the efficacy analysis as recommended for noninferiority trials [32]. The incidences of TLP and PDPH as well as the first puncture success rate between the respective study arms will be compared with the Chi-squared test. The 95% confidence intervals (95% CI) for the difference will be calculated using the exact Clopper-Pearson method. Between-arm comparisons of blood and CSF data, other performance parameters, and incidences of other complications will be performed for descriptive purposes. Definitions of the outcome variables to be used in the efficacy analysis are presented in Table 2 in terms of domain, measurement, metric, aggregation, and time point according to a recommended framework for clinical trials [33, 34]. In case of missing data, data estimation nor imputation will not be performed.

**Table 2 Tab2:** Definitions of the outcome variables (only those domains pertinent to the efficacy analysis are presented) in terms of domain, measurement, metric, aggregation, and time point

Domain	Specific measurement	Metric	Method of aggregation	Time point
Incidence of TLP	Flow cytometry	Erythrocyte count ≥ 10/µL (yes/no)	Proportion	Each study LP procedure
First puncture success rate	Provider’s self-report on CRF	Occurrence (yes/no)	Proportion	Each study LP procedure
Incidence of PDPH	Symptom diary	Occurrence (yes/no)	Proportion	Within 1 week after each study LP procedure
Peripheral blood analysis	Flow cytometry	Erythrocyte count (cells/µL) Hematocrit (%) Hemoglobin (g/L) Leukocyte count (cells/µL) Thrombocyte count (cells/µL) Existence of blasts (yes/no)	Mean Mean Mean Mean Mean Proportion	Each study LP procedure
CSF analysis	Flow cytometry	Erythrocyte count (cells/µL) Leukocyte count (cells/µL) Existence of blasts (yes/no)	Cumulative distribution curve Mean Proportion	Each study LP procedure
Number of LP attempts	Provider’s self-report on CRF	Number	Median	Each study LP procedure
Number of failed procedures	Provider’s self-report on CRF	Occurrence (yes/no)	Proportion	Each study LP procedure

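### The provider may exclude a single LP from the study after the alternating needle sequence is known, so inclusion in the trial can depend on the needle due

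*Protocol article*

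**What the plan says.** All references are to the protocol article.

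- **Who decides.** Recruitment and consent ends with "The final decision to include or exclude the patient or a single LP procedure (e.g., the initial procedure of the patient with ALL"), a decision that "will be up to the clinical judgement of the provider". No closed list of reasons is attached.
- **Listed procedure-level exclusion.** The same section excludes an LP when "There is any temporary contraindication to LP, including but not limited to skin infection around the puncture area" and similar conditions apply. The list is open-ended, but none of its items depends on the needle.
- **When the needle becomes known.** Under Randomization and allocation, on enrolment "the next available envelope in the order will be opened to reveal the sequence of study LP procedures for the given patient". Trial design and setting adds: "Thus, the two possible randomly assigned sequences of the study LP procedures are ABAB and BABA".
- **Who is blinded.** Procedures states: "Because of general anesthesia, the patient is blinded to the allocated spinal needle". No blinding of the provider is claimed. Of the IQ-Tip needle, The LP procedure A says: "Only the cable at the handle end is the major difference". The system also has an analyzer and gives an audio-visual alarm.
- **Related safeguards.** Other outcomes counts a provider's choice of a needle other than the assigned one as a failed procedure, reported for both arms. Monitoring lists a check that study LPs follow the allocated order with the proper needle, and protocol violations are registered.
- **Analysis.** Under Data analysis, "per-protocol analysis will be employed in the efficacy analysis as recommended for noninferiority trials".

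**The concern.** Randomisation protects the comparison only if the choice of procedures that enter it does not depend on the arm. Here a procedure-level decision can be taken after allocation, by someone who knows the arm, on grounds that are not limited to the listed contraindications. If LPs expected to be hard are left out more often when one needle is due, that arm's TLP incidence is lowered by selection alone.

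An analysis of the collected data could not repair this, because the omitted LPs would not be in the data. A short series would not look unusual either, since two to four procedures per patient are allowed. The primary conclusion is at stake: a noninferiority claim with a 5-point margin and about 150 procedures per arm.

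**Working it through.** **1. Is there a route that the safeguards miss?** Take an LP that goes ahead clinically in an enrolled patient when IQ-Tip is due.

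| What the provider does | Record under the article |
|---|---|
| Keeps it as a study LP, uses IQ-Tip | Arm A procedure |
| Keeps it as a study LP, uses another needle | Failed procedure, reported by arm; order and needle are monitored |
| Declares it outside the study beforehand, uses another needle | None described |

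The second and third rows can be the same puncture with the same needle. The failed-procedure rule and the inclusion rule classify it differently, and nothing says which prevails. The same table holds with the arms exchanged.

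**2. The plan's own figures.** Sidedness is not stated. With 20% against 30%, a 5-point margin, 150 per arm and one-sided 0.05, the power is 91.5%, close to the stated 90% (85.5% at one-sided 0.025). The upper 95% one-sided Wald limit reproduces the stated threshold: 26/150 against 30/150 gives 4.73 points (noninferior), and 26/150 against 29/150 gives 5.35 (not). One-sided 0.05 is therefore used below.

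**3. Risk after a failed first attempt.** The article does not state it. It follows from 17.3% TLP overall (Data analysis), 80% first-puncture success and about 11% TLP after success (Discussion):

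(0.173 − 0.80 × 0.11) / 0.20 = 0.085 / 0.20 = 42.5%.

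This is 3.9 times 11%, in line with the fourfold figure in the Background.

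**4. Shift in arm A.** If a share f of arm A procedures with risk r is left out, the observed incidence is (0.173 − f·r) / (1 − f). Both f and the value r = 25% are assumptions.

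| r | f | Observed A | Shift |
|---|---|---|---|
| 42.5% | 5% | 0.15175/0.95 = 16.0% | −1.3 points |
| 42.5% | 10% | 0.1305/0.90 = 14.5% | −2.8 points |
| 25% | 5% | 0.1605/0.95 = 16.9% | −0.4 points |
| 25% | 10% | 0.148/0.90 = 16.4% | −0.9 points |

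The value of 42.5% is a ceiling. It is the risk given that the first attempt failed, which is known only after the puncture, so it assumes that the provider foresees every failure.

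**5. Effect on the error rate.** Let the true rates lie exactly at the margin: A 17.3%, B 12.3%, with 150 analysed procedures per arm, treated as independent. The standard error is √(0.173 × 0.827/150 + 0.123 × 0.877/150) = 0.0409. The false noninferiority rate is approximately Φ(−1.645 + shift/0.0409), with the size of the shift put in. It is 5% without exclusions. For shifts of 0.4, 0.9, 1.3 and 2.8 points it is about 6%, 8%, 9% and 17%.

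**6. Sensitivity near the threshold.** 27/150 against 30/150 fails (upper limit 5.45 points), while 26/149 against 30/150 passes (4.87). At that point, leaving out one arm A procedure that would have been traumatic changes the conclusion.

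**The case against.** Several arguments against the point have weight.

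- **Narrow reading.** The sentence follows the exclusion criteria and may only name who applies them. Its one example, the initial LP in ALL, may be settled before enrolment, where it does no harm. This is plausible, but the wording is not restricted to it. The example is also not a contraindication; it is an LP that may be performed outside the study.
- **Existing safeguards.** A reader might infer that a diverted LP always vanishes without trace. The article does not support that: a needle switch in a study LP is a reported failure, and order and needle are monitored. The gap is confined to LPs declared outside the study beforehand.
- **Direction.** A reader might also infer that the rule favours IQ-Tip. Nothing in the article shows which arm would lose procedures. The Discussion reports that some users had concerns about the cable and the alarms, which makes avoidance of IQ-Tip conceivable, but exclusions from arm B would bias the comparison the other way.
- **Foresight.** In the earlier single-arm study, neither success nor TLP was associated with provider experience or patient overweight (Background). This argues against good prediction of hard punctures and for the smaller shifts.
- **Condensed source.** The CRFs and the dated monitoring plan are not shown. An exclusion log may exist, so its absence is not the finding. The stated inclusion rule, and its conflict with the failed-procedure rule, remain.

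**Conclusion.** The point stands as a design weakness, not as a demonstrated bias. The stated rules allow a provider who knows the due needle to decide whether a single LP belongs to the trial. One class of LPs, those performed but declared outside the study beforehand, falls between the inclusion rule and the failed-procedure rule.

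If exclusions fell on arm A only, at assumed rates of 5% and 10%, the shift would be at most about 1.3 and 2.8 points, and about 0.4 and 0.9 points at a more modest assumed risk. Exclusions from arm B would act in the opposite direction, and balanced exclusions would largely cancel. The size cannot be fixed from the article, because neither the exclusion rate nor the risk of excluded LPs is known.

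It would be tempting to conclude that the per-protocol analysis should give way to an as-allocated one. That does not follow. Counting conventional-needle LPs in arm A can dilute a true difference, which itself favours noninferiority.

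**What to change.** The clinical decision whether to perform an LP stays with the provider. Only its consequence for the study needs rules.

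1. Decide and record whether the initial LP belongs to the study before the envelope is opened.
2. After allocation, log every LP that is skipped, excluded or done with another needle, with the due needle and the reason, and report the counts by arm. If the CRFs or the monitoring plan already contain such a log, refer to it and add it to the listed monitoring checks.
3. Reconcile the inclusion rule in Recruitment and consent with the failed-procedure rule in Other outcomes, so that an LP performed within the patient's study series has one classification.
4. Retain the routine CSF erythrocyte count of LPs performed within the series. Add a supportive analysis by allocated needle beside the per-protocol analysis, and require consistent conclusions from both before noninferiority is claimed.

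The cost is a short amendment and a brief log. The CSF count is already routine, so no procedure or test is added. The downside is the possible dilution in the as-allocated analysis, which is why it supplements the per-protocol analysis and does not replace it.
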